## 5. METHODOLOGY

### A. Participants

- We plan to recruit a total of 100 participants.
- Participants will be chronic (>3 months post stroke) left-hemisphere stroke survivors, ages 18-85. Potential participants will be identified through review of hospital admissions at the Kessler Institute for Rehabilitation. Additionally, potential participants will be identified through the Adler Aphasia Center, the Kessler Foundation Subjects Information Management System (SIMS), or by referral from the Recruitment Specialists at Kessler Foundation, the Investigators involved in the study, or referrals from other sources. Those with a diagnosis of left-hemisphere stroke will be approached for recruitment. A PI or the research assistant will initiate verbal communication with the participant and/or their family members. Participants who indicate research interest and meet the inclusion criteria will be asked to participate.
- **Inclusion Criteria** for participation will be: having English as first language, basic capacity to understand and execute the experimental tasks, age between 18-85, and diagnosis of left-hemisphere stroke >3 months. Participants will be assessed for reading deficits using self-report and standardized assessment.
- **Exclusion Criteria** for participation will be: contraindication to MRI, such as claustrophobia, pregnancy, extreme obesity, inability to lie flat, implanted ferromagnetic devices; and other exclusion criteria, such as uncorrectable hearing or vision difficulties, psychiatric illness, or learning disability. In addition, degenerative neurological disorders (Alzheimer's or Parkinson's disease) and previous brain injuries will be exclusions. We will also exclude participants if they have contraindication to exercise, as this would preclude them from completing all study tasks. All participants will be required to fill out the PARQ+ questionnaire (Warburton et al., 2011) to assess their readiness for physical exercise. Participants identified as having a moderate to high risk of contraindications to

exercise, and those for whom their physician cannot provide clearance for exercise, will be excluded from the study. Finally, the patient cannot participate if they were left-handed prior to their stroke or if they are undergoing a one-on-one speech and language therapy that overlaps in content with the tested treatment. No exclusion will be made on the bases of race, ethnicity, or gender.

- **Potential risks** to patients may include fatigue from completing neuropsychological testing and participating in MRI sessions. To protect against such risks, behavioral tests will be targeted to last one hour (but will not exceed 2) and will be administered at a time when the patient is not involved in therapy. MRI scanning will take place in the same building as inpatient care requiring minimum transportation and will last no longer than 1 hour. There are no known significant risks or side effects associated with MRI scans when all scanning parameters remain within FDA guidelines and when all participants with contraindications for MRI are excluded. The study will adhere to the FDA regulations and to the inclusion and exclusion criteria. Potential discomforts include feelings of claustrophobia and discomforts associated with considerable background noise generated by the MRI scanner (approximately 120 dB peak SPL). Participants will be screened for prior history of severe claustrophobia and during the scan all participants will be wearing earplugs to protect their hearing. Moderate intensity exercise may be associated with an increased risk of musculoskeletal injury, irregular heart rhythms, and shortness of breath. To safeguard against these risks, we will exclude participants who have moderate to high-risk contraindications for aerobic exercise. Additionally, all aerobic training sessions will be supervised by trained staff. Heart rate will be monitored continuously to ensure that the participants stay within the prescribed exercise intensity limits. The proposed aerobic exercise intervention (5 days/week of 20 mins of moderate intensity, 60-70% of heart rate range) approximates public health guidelines for aerobic activity (i.e., 150 mins/week of moderate or 75 mins/week of vigorous activity). Furthermore, numerous studies demonstrated beneficial impact of exercise on physical and cognitive metrics (Lefferts et al., 2019; Mayer et al., 2021; Northey et al., 2018; Zheng et al., 2016)
- The research staff will follow rigorous ethical protocols established at Kessler Foundation Stroke Laboratory for the protection of patients' rights and **confidentiality**. The research materials, consisting of MRI images, behavioral and questionnaire data, will be securely stored on password-protected computers in locked laboratory space. Each data file will be numbered and will have no information about the identity of the patient. The written informed consents will be kept in a locked cabinet. Only the research staff listed on the application will have access to the file identifying each patient's numeric code. The file will be kept in a secure location for the purpose of sharing the results of participant's own performance upon his/her request. After data collection is complete, the data will be available to the PIs, Co-I, and SC for review. Descriptive and inferential

statistics generated from the data will be used for further research and scientific dissemination.

- The PIs will ensure that patients are informed about the outcome of the study, as well as about their own performance, upon their request. Each patient undergoing neuroimaging will be provided with a screenshot picture of his or her brain and a full electronic copy will be provided upon request. Participants will complete 3 MRI scans (before treatment, after a single AET session, and after treatment). They will receive 60 hours of reading treatment. In addition, they will complete 20 minutes of moderate intensity cycling (prescribed individually based on heart rate) or light stretching prior to each reading treatment session. To cap treatment session duration at 2 hours, we will administer this treatment in 40 sessions. They will be paid \$100 for their participation, with payment prorated (\$50 for completing behavioral and physical assessments and 2 MRI scans; \$50 for completing assessments, therapy, and the final MRI scan).
- Patients who indicate research interest and meet the inclusion criteria will be asked to provide a written informed consent prior to any behavioral testing or MRI scanning. A copy of the informed consent is attached.

## B. Research Procedures

- Following screening, participants will be randomly assigned to one of 2 exercise conditions: aerobic exercise (cycling) or control (light stretching).

Participants will then undergo baseline assessments, treatment, and outcome assessment. They will also complete 3 MRI scans as detailed below.

- Patients will be tested for phonological, orthographic, and semantic impairments using a two-alternative forced choice touch-screen paradigm (Boukrina et al., 2020). On semantic trials, the target is a concrete noun presented at the top of the screen. The two choices on the bottom include a close semantic neighbor that has high feature similarity to the target and a more distant semantic neighbor. Patients are instructed to select the word that is most similar in meaning to target (Fig.1). On phonological tasks, all letter strings are pseudowords and the task is to select the string that rhymes with the target at the top. The choices include a close rhyme of the target with non-matching orthography and a close, but implausible rhyme. There are both a word and a picture version of these tasks. In the orthographic task, all letter strings contain consonant doublets that are part of a trigram with high or low (position-constrained) frequency. Participants are asked to identify which string looks more like it could be a word (task and stimuli adapted from Cassar &

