## **RESEARCH PROTOCOL R-1242-23**

### **IMPROVING READING COMPETENCE IN APHASIA WITH COMBINED EXERCISE AND PHONO-MOTOR TREATMENT**

#### **EXECUTIVE SUMMARY AND ADMINISTRATIVE INFORMATION**

The study will recruit participants at the Kessler Institute for Rehabilitation (KIR) and other sources as detailed in the application, where our Stroke research team has been collecting very detailed information about left-hemisphere stroke patients, including the patients' mental function, and reading ability. The left-hemisphere stroke patients who meet the following inclusion criteria will be enrolled in the study:

1. Fluent and proficient in English prior to stroke
2. Left hemisphere stroke >3 months ago
3. Age range 18-85
4. Reading deficit as established through self-report and formal testing

The participants are excluded from the study if they have any other neurological disorders, if they have contraindications to MRI, or if they have a vision problem that interferes with reading, if they are unable to participate in exercise or if they are currently undergoing one-on-one speech and language therapy.

Participants will complete a total of 60 hours of reading therapy. In addition, they will engage in 20 min of aerobic exercise (cycling) or stretching prior to each treatment session along with 5-min warm up and cool down. Session duration will be capped at 2 hours, participants will complete a total of 40 sessions (30 min exercise + 90 min reading therapy per session). Participants will also undergo an MRI at baseline, on day 1 of assessments, following 30 minutes of cycling or stretching, and after treatment. Participants will be compensated \$100 for their participation.

The main goal of this study is to improve the current understanding of brain mechanisms for reading and to develop effective, evidence-based treatments for post-stroke reading deficits. A left-sided stroke often results in language and reading disabilities, where individuals encounter challenges effectively returning to work and performing basic daily tasks. This study may help to alleviate the burden of reading disabilities.

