- The behavioral data collection will be primarily carried out by the research assistants closely monitored by the PIs. [name] will monitor IRB compliance and assist with day-to-day needs of the project. MRI data collection will be completed under close supervision of the PI, [name]. The data will be transferred to the password protected computers in a locked laboratory for review and analysis. Following analysis, study results will be prepared for publication. At that time, patients will be informed about the outcome of the study. Upon request, participants will also be informed about their own behavioral results once they complete their participation in the study.

We anticipate that we may uncover novel demographic or other subject data associations related to reading ability as we proceed. We will ask subjects' permission to contact them by telephone or visit them in person on the rare occasion that additional demographic data needs to be collected.

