#### Univariate analyses:

*Behavioral data:* To measure the impact of treatment we will use a 2x2 repeated measures design assessing whether participants in the AET+PMT condition improve more from baseline to outcome than those in the Stretching+PMT condition. The reading tests (RCBA, reading aloud, touchscreen tests) will serve as primary outcomes and other language tests (WAB-R, PNT, CAT-DQ) as secondary outcomes. Improvement would be indicated by a significant condition by session interaction. We will also evaluate the within-subjects effect of PMT on reading improvement (post-treatment > baseline).

*Cerebral Blood Flow (CBF) data:* To examine the immediate effect of aerobic exercise on cerebral hemodynamics we will compare CBF measured with Arterial Spin Labeling (ASL) scans (used to measure cerebral circulation) at baseline (T1) with CBF measured after 20 min of moderate to vigorous intensity aerobic exercise (or 20 min of light stretching, T2).

ASL provides a non-invasive absolute (mL (blood volume)/100g (tissue volume)/min (time)) measure of CBF, that is suitable even for patients who may have impaired kidney function and cannot undergo contrast-based perfusion MRI (Zaharchuk, 2014). In ASL, water molecules are labeled with a magnetic pulse before they enter the brain through the arterial blood supply. The effect of labeling can be quantified by characterizing the interaction of blood flow and label decay. (Detre et al., 1998, 2012) Thus, ASL will be used to provide a measure of CBF changes as a function of AET. It is well known that stroke and cardiovascular disease can cause deficits in temporal dynamics of blood flow (Roc et al., 2006; Treger et al., 2007). Furthermore, Altamura et al. (Altamura et al., 2009) reported that delays in the hemodynamic signal are associated with worsened cerebral autoregulation (maintenance of constant blood flow despite changes in arterial blood pressure). For this reason, in addition to changes to regional and global CBF, we will evaluate the spatial coefficient of variation (sCoV) in the ASL signal as an indirect measure of arterial transit time, as proposed in Mutsaerts et al. (Mutsaerts et al., 2017), because prolonged transit times lead to proportion of the ASL signal remaining in conduit arteries at the time of

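### Randomisation precedes the baseline assessments, and the protocol does not say that allocation is withheld until baseline is complete

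*Protocol*

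**What the plan says.** Section 5.B (Research Procedures) sets the order. First, "Following screening, participants will be randomly assigned to one of 2 exercise conditions". The next sentence reads: "Participants will then undergo baseline assessments, treatment, and outcome assessment". No other part of the protocol places a baseline test before randomisation. None says that allocation is held back from participants or testers until baseline testing is done.

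Section 5.C (Univariate analyses) states that "The reading tests (RCBA, reading aloud, touchscreen tests) will serve as primary outcomes" and that "Improvement would be indicated by a significant condition by session interaction". The design is a 2x2 repeated-measures comparison from baseline to outcome. Section 5.C also requires both the intent-to-treat and the per-protocol analysis to support superiority.

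On testers, section 5.B says: "The behavioral data collection will be primarily carried out by the research assistants closely monitored by the PIs".

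On eligibility, the Executive Summary lists "Reading deficit as established through self-report and formal testing" among the inclusion criteria, and section 5.A says: "Participants will be assessed for reading deficits using self-report and standardized assessment". Neither place names the test or says when it is given. The RCBA-2, the standardised reading battery that the protocol names, is described in section 5.B after the randomisation sentence.

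**The concern.** In a change-from-baseline comparison the baseline score counts as much as the outcome score. If it is collected after assignment, and the participant or tester knows the arm, then effort, expectation or scoring can differ between arms before any treatment is given. Reading aloud leaves some room for this. The two-choice touchscreen task leaves less room for scoring judgement but still depends on effort. A baseline that is too low in the cycling arm, or too high in the stretching arm, looks like a benefit of exercise. The opposite shift would hide a real benefit.

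The second consequence concerns the analysis set. A participant who withdraws after randomisation but before baseline has been randomised and has no baseline value. An analysis of complete baseline-outcome pairs cannot include that person.

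The covariate rule in section 5.B does not help. It covers depression, neglect and cognitive screening, not the baseline reading scores. Once a baseline has been measured under knowledge of the arm, analysis cannot recover one that was not.

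**Working it through.** **Order of procedures.** Section 5.B gives screening, then random assignment, then baseline assessments, treatment and outcome assessment. The baseline values in the interaction of section 5.C are therefore collected after assignment.

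**How a baseline shift enters the effect.** Write the mean scores as Y0 (baseline) and Y1 (outcome) for the cycling arm (A) and the stretching arm (S).

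- Interaction = (Y1A − Y0A) − (Y1S − Y0S).
- If Y0A is lowered by b and nothing else changes, the interaction rises by exactly b.

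**Illustrative size.** The protocol shown gives no SD, correlation, alpha or power, so there is no stated figure to reproduce. Inputs:

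- From the protocol: 100 participants in total (section 5.A).
- Assumed: equal split, so n = 50 per arm; two-sided alpha 0.05 (critical value 1.96); no true effect; equal SDs; pre-post correlation r of 0.5, 0.7 or 0.9; differential baseline shift b of 0.1, 0.2 or 0.3 SD.

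Formulae, in SD units, by normal approximation:

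- SE = sqrt(2(1 − r)) × sqrt(2/n)
- False-positive rate = 1 − Φ(1.96 − b/SE) + Φ(−1.96 − b/SE)

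Standard errors:

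- r = 0.5: sqrt(1.0) × sqrt(0.04) = 0.200
- r = 0.7: sqrt(0.6) × sqrt(0.04) = 0.155
- r = 0.9: sqrt(0.2) × sqrt(0.04) = 0.089

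One case in full, r = 0.7 and b = 0.2: b/SE = 0.2/0.155 = 1.29, so the rate is 1 − Φ(0.67) + Φ(−3.25) = 0.252.

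| Assumed r | b = 0.1 SD | b = 0.2 SD | b = 0.3 SD |
|---|---|---|---|
| 0.5 | 7.9% | 17.0% | 32.3% |
| 0.7 | 9.9% | 25.2% | 49.1% |
| 0.9 | 20.1% | 60.9% | 91.8% |

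With b = 0 the rate is 5% in every row. A given shift does more damage at a higher correlation, because the change score is then more precise.

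**Eligibility test.** The Executive Summary and section 5.A make formal reading assessment part of inclusion, and section 5.B randomises after screening. Section 5.A also has patients who already meet the inclusion criteria give consent before any behavioural testing, although a formal test is itself a criterion. These passages do not settle when the test is done.

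**The case against.** The strongest reply is that assigned does not mean disclosed. The bias needs someone to know the arm at baseline, and the protocol never says that anyone does. Participants cannot be blind to cycling versus stretching once the first bout begins, but sections 2 and 5.A put the baseline scan before that bout. This stands, and it makes the point conditional. It does not remove it, because nothing in the protocol provides for concealment through baseline. The Executive Summary's MRI schedule can also be read as placing the assigned bout on the first assessment day. Its punctuation is ambiguous, but on that reading the arm would be evident while some baseline tests might still be outstanding.

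It is also fair that the correlation and the shift are assumptions, that the document gives no reason to expect a shift in either direction, and that losses between allocation and baseline are not quantified. All of this stands.

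A reader might infer that the reading-deficit test is done after randomisation, so that people without a deficit are randomised. The documents do not support this. Screening may include the test, section 5.B is arranged by instrument rather than by time, and the Executive Summary says that the team already holds reading data on left-hemisphere stroke patients. What remains is an unnamed test and an unstated time point.

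A reader might also take the tester sentence as evidence about blinding at outcome. That is a separate matter, which reordering would not solve, and it is not part of this point.

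**Conclusion.** The order is explicit: primary-outcome baselines are measured after assignment, with no stated concealment. A differential baseline shift would enter the primary effect in full, and early leavers would have no baseline value. This is a risk of bias, conditional on the arm being known at baseline, and not evidence that bias will occur. The true shift may be zero. The tabulated rates, from about 8% to 92%, show only how sensitive the test is under the assumed correlations and shifts; none is an estimate for this trial. Confidence is high for the sequence and limited for its consequences. The point should be fixed, because the remedy is cheap and a contaminated baseline cannot be repaired afterwards.

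**What to change.** Change section 5.B so that the eligibility reading test, all baseline behavioural tests and the baseline MRI are completed before randomisation, and allocation is disclosed just before the first cycling or stretching bout. If the order cannot change, state that allocation is concealed from participants and testers until baseline is complete. Concealment alone limits the bias but still leaves randomised participants without a baseline if they withdraw early.

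In section 5.A, name the formal reading test that establishes eligibility and state that it is done at screening.

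The tests and scans stay the same. Assignment would be known slightly later for scheduling. Because section 5.A caps behavioural testing at 2 hours and the battery is long (the cognitive screen alone is listed at 1 hour), baseline testing may need to be spread over visits before the first bout.

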### Semantic      Phonological      Orthographic

|                |                |                |
|----------------|----------------|----------------|
| goose          | gake           | beff      ffeb |
| lamb      swan | daik      jeak |                |

Figure 1. Example trials in the behavioral task administered to patients.

Treiman 1997). Patients will also complete a reading aloud task, in which they will be asked to read single words, with varying lexical characteristics, as well as pseudowords.

- Patient demographics will be collected using a self-report questionnaire. The PI will assist patients in completing the questionnaire and where necessary will contact family members for additional information.
- Participants will complete the Reading Comprehension Battery for Aphasia (RCBA-2nd edition), and, additionally, will complete will include the Western Aphasia Battery, Revised (WAB-R) (Kertesz, 2007), the Philadelphia Naming Test (PNT) (Walkera and Schwartz, 2012), and self-reported ratings of language disability from the Comprehensive Aphasia Test Disability Questionnaire (CAT-DQ) (Swinburn et al., 2004) .
- We will also assess depression via the Geriatric Depression Scale (Yesavage et al., 1982) (5 min), spatial neglect via the Behavioral Inattention Test-conventional(Halligan et al., 1990) (15 min), and screen for other cognitive deficits using the Oxford Cognitive Screen (OCS) (Demeyere et al., 2015) (1 hour). If found different between conditions, these tests will be used as covariates when examining the effects of intervention on behavioral and neural outcomes. A 10-meter walk test (Moore et al., 2018) and a 6-min walk test (Kosak and Smith, 2005) will be administered to measure the impact of the AET and stretching interventions on mobility (gait speed and walking distance).
- They will undergo 3 MRIs, including structural, perfusion, and functional sequences. Each scan will last approximately 50 minutes. The results of the scans will be used to determine the size and location of the stroke lesion, and the impact of treatment on cerebral blood flow and function. Participants will undergo 40 sessions of treatments (2 hours each). The treatment will start with 20 minutes of aerobic exercise (cycling) or stretching preceded and followed by 5 minutes of warm up and cool down. Participants' heart rate will be monitored continuously, and those undergoing aerobic exercise will be asked to exercise at a heart rate equal to 60-70% of their individual maximal heart rate (i.e., moderate intensity). Aerobic exercise will be supervised by a senior scientist with physical therapy and exercise research expertise ([name]). The exercise will be followed by 1,5 hours of reading therapy (Phono-motor treatment) (Kendall et al., 2019). The treatment fidelity will be monitored by the co-I, [name], who will review randomly selected treatment session videos at a rate of ~1 video/week/participant.
- Some participants may not complete all sessions according to the proposed schedule due to unforeseen circumstances (such as participant or staff illness, transportation problems, etc.) or because of holidays or other commitments. Efforts will be made to reschedule missed sessions as close to the original proposed dates as possible. The total length of the intervention period may also be extended if needed to provide time to reschedule missed sessions.
- In addition to assessing the rate of perceived exertion during each 5-minute exercise interval, we will ask participants to rate their enjoyment, willingness to continue to engage in the exercise program, and difficulty adhering to the program at the end of each

exercise session. We will also prompt participants for free form comments about their experience in the program.

- The behavioral data collection will be primarily carried out by the research assistants closely monitored by the PIs. [name] will monitor IRB compliance and assist with day-to-day needs of the project. MRI data collection will be completed under close supervision of the PI, [name]. The data will be transferred to the password protected computers in a locked laboratory for review and analysis. Following analysis, study results will be prepared for publication. At that time, patients will be informed about the outcome of the study. Upon request, participants will also be informed about their own behavioral results once they complete their participation in the study.

We anticipate that we may uncover novel demographic or other subject data associations related to reading ability as we proceed. We will ask subjects' permission to contact them by telephone or visit them in person on the rare occasion that additional demographic data needs to be collected.

